#### School recruitment and randomization

2.4.1

In Phase I, a convenience sample of approximately 50 students will be recruited. A call to action will be used to engage adolescents through the development of infographics and information about the aims of this phase, which will be disseminated through social media, personal contacts, or emails. Since these tests will be conducted outside the school timetable, no schools will be directly contacted. Instead, parents or legal guardians will be responsible for contacting the research team if their children are interested in participating in the study and they provide their consent. In this call to action, incentives, such as activity wristbands will be given away to participating adolescents. For Phase II, a specific selection protocol will be implemented through a random draw. A list of all public secondary schools in each of the participating cities of the government educational institutions in Andalucía will be obtained. The schools in the three cities (Granada, Almería, Jaén) will be contacted by phone, and if they are interested in participating, they will have to meet a series of inclusion and exclusion criteria presented in Table 1. During the call, a meeting will be arranged with interested schools to explain to the management team and teaching staff the main objective of the study, as well as to obtain official consent to participate in the project from the school. After that, the research staff with the help of Physical Education teachers will recruit participants and their families, by visiting selected classes and explaining the study to prospective adolescent participants and finally requesting the family’s consent. The inclusion and exclusion criteria for the participants are presented in Table 2. To complete the sample of students in the intervention group, several schools may be needed, as not all students will be able to participate in the school-based cycling intervention due to family reasons, distance, predisposition, etc. To encourage as many students as possible from the intervention school to participate (with their families’ consent) in the school-based cycling intervention, an incentive system will be planned similar to other studies (42, 43). This incentive will consist of a voucher to be redeemed for sports equipment, provided that the participant has completed the 8 weeks of intervention and presents valid data at both baseline and follow-up. Once finished the baseline assessment, the participating schools will be randomly assigned through a draw to either a control or experimental group.

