
**Table 1 tab1:** Schools’ inclusion and exclusion criteria.

Inclusion criteria	Exclusion criteria
The school has a specific space for parking bicycles and allows their parking	The school does not have specific infrastructure to park or store bicycles
The school has at least two classes per grade	The school offers bus transportation to the adolescents
At least eight students from the school will agree to participate in the study	The school is already participating in other interventions focused on promoting healthy behaviors
Schools from urban areas	The school has implemented an intervention to encourage commuting to school within the last year
	Schools from rural areas

**Table 2 tab2:** Participants’ inclusion and exclusion criteria.

Inclusion criteria	Exclusion criteria
Adolescents’ females and males aged from 12 to 17 years old (both ages included)	Adolescents younger than 12 years or older than 17 years
Healthy participants who can ride a bicycle safely and without difficulty.	Participants with any injury or medical condition that prevents safe participation in cycling to and from school
Be able to cycle to and from school at least 3 days per week during eight consecutive weeks (Intervention group)	Insufficient ability to ride a bicycle or inability to cycle to and from school at least 3 days a week (Intervention group)
Not to cycle to and from school more than 3 days a week during the last year	Participants who have cycled to and from school more than 3 days a week during the past year
To present a valid signed consent from their parents or legal guardians	Participants without a valid, signed parental or guardian consent form
To present valid data at baseline and follow-up from all the outcomes assessed	Participants who do not provide valid data for all assessed outcomes at baseline and follow-up

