##### School characteristics

2.7.2.20

School characteristics will be assessed using various measures. School size will be determined based on student enrollment, reflecting the total number of students enrolled during the study period. School socioeconomic status (SES) will be established using data from previous studies (91). Additionally, the socioeconomic status of the school neighborhoods will be objectively analyzed and classified as high or low using GIS. Moreover, the length of the cycling lane network within a 5.1 km street-network buffer around each school will be calculated using GIS (92). Additionally, school staff will be asked to provide information on the availability of bicycle racks either on school premises or near the main entrance. School engagement, which may influence the effects of the intervention, will be assessed through the perceptions of the research staff. Engagement will be categorized into three dimensions: teacher engagement (average staff perceptions of teacher involvement across all classes), student engagement (average staff perceptions of student participation across all classes), and overall school engagement (average of teacher and student engagement scores). Data for all variables will be collected during baseline and follow-up assessments and aggregated by participant and school.

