#### Statistical analysis

2.10.2

Descriptive analyses of all study variables presented with the mean (standard deviation) and frequencies (percentage) will be performed. Subsequently, the normality of the variables will be analyzed using histograms and normality tests. In Phase I, for the comparison of PAEE between the different modes of commuting (i.e., walking, cycling, and motorized-vehicle), a repeated measures ANOVA will be performed using the per-protocol approach. In addition, Student t-test or Mann–Whitney tests will be performed to compare the fluctuation of PAEE according to speed or distance commuted between active modes of commuting (i.e., walking vs. cycling).Within Phase II, the effects of the school-based cycling intervention on RMR and other health-related outcomes will be studied using an analysis of covariance (ANCOVA). Post-intervention RMR and other-health related values will be included as dependent variables, group (i.e., experimental group vs. control group) as fixed factor, and baseline outcome data as covariates. To evaluate the effect of the intervention on the secondary outcomes (i.e., physiological, physical, and psychosocial outcomes), we will conduct the same analysis used for the main outcomes (i.e., ANCOVA analysis using the intention-to-treat approach). Moreover, to control the variability between schools, the analyses will include adjustments for contextual and organizational variables, such as the SES of the school area, the length of cycling lanes, the availability of bicycle parking, and the level of engagement of teachers and students in the intervention. The estimates will be present as raw and standardized (z-scores; i.e., mean differences between follow-up and baseline data divided by the standard deviation), as an indication of the change the post-intervention z-scores will be calculated relative to the baseline mean and standard deviation. Effect sizes will be categorized as small (0.2 SDs), medium (0.5 SDs), and large (0.8 SDs), based on Cohen (93). Finally, to analyze the influence of covariates on the association between the intervention and the main outcomes (i.e., RMR and PAEE), mediation analyses will be performed. The intervention will be included as the independent variable, and the main outcomes as the dependent variables. Covariates included in the mediation analysis will encompass body composition, physical function, cognitive determinants, perceived barriers or autonomy, built-environment characteristics, weather, among others. In the statistical analysis, a value of *p* < 0.05 will be considered statistically significant.

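### The effect analyses adjust for engagement in the intervention, which as worded is a consequence of allocation and can bias the group effect

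*Protocol article*

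**What the plan says.** The Phase II effect model in section 2.10.2 (Statistical analysis) is an ANCOVA of the post-intervention value, with "group (i.e., experimental group vs. control group) as fixed factor, and baseline outcome data as covariates". The same paragraph adds that "to control the variability between schools, the analyses will include adjustments for contextual and organizational variables". Besides area socioeconomic status and cycling-lane length, the adjusters named there are "the availability of bicycle parking, and the level of engagement of teachers and students in the intervention".

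Four other places bear on this list:

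- **Timing of the draw** (section 2.4.1): "Once finished the baseline assessment, the participating schools will be randomly assigned through a draw to either a control or experimental group".
- **Engagement** (section 2.7.2.20): "School engagement, which may influence the effects of the intervention, will be assessed through the perceptions of the research staff". That section closes with: "Data for all variables will be collected during baseline and follow-up assessments and aggregated by participant and school".
- **Control schools** (section 2.5): pupils keep to their usual habits during the eight weeks, and the schools are offered the training and motivational material afterwards.
- **Parking** (Table 1): a school is eligible only if "The school has a specific space for parking bicycles and allows their parking". Lack of bicycle parking infrastructure is also an exclusion criterion.

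On mediation, section 2.10.2 states: "Covariates included in the mediation analysis will encompass body composition, physical function, cognitive determinants, perceived barriers or autonomy, built-environment characteristics, weather, among others".

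**The concern.** A covariate in a randomised comparison is safe when allocation cannot have affected it. Engagement of teachers and pupils in the intervention, read as written, does not meet that condition. There is nothing to engage with until a school has been allocated to the programme, and in control schools there is no programme to engage with during the comparison period. The protocol also puts engagement on the causal path, since section 2.7.2.20 says it may influence the effects. The rating comes from research staff, and section 2.8 has the research group delivering the training sessions, so the score is unlikely to be independent of knowledge of the arm.

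Two things follow if it is adjusted for. The group coefficient no longer estimates the total effect of allocation, because whatever works through engagement is taken out. In addition, any unmeasured school factor that raises both engagement and outcome becomes a source of bias that randomisation would otherwise have balanced on average. The adjustment is written for the analyses in general, so it reaches RMR and PAEE as well as the secondary outcomes.

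Two lesser faults sit in the same paragraph. An adjuster that every enrolled school shares does no work, and a mediation analysis that lists variables allocation cannot change needs to say what role they play.

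**Working it through.** The plan states no figure on this point, so there is none to reproduce. The check has three parts.

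**1. Is the engagement adjuster a post-allocation variable?** Baseline assessment comes first, then the draw (2.4.1), then eight weeks in which only intervention schools have a programme (2.5). Engagement is rated at baseline and again at follow-up (2.7.2.20). Section 2.10.2 does not say which rating is used. Its wording, engagement in the intervention, fits the later rating and not one made before any school had a programme.

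**2. What would adjusting for it do?** Every value here is assumed; none is in the protocol. Let T be arm (0 or 1), and let engagement be E = aT + e with SD 1 within arm. Let the true total effect be 0.50 SD, with a share s of it running through E. The adjusted group coefficient is then (1 − s) × 0.50:

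| Share s | Arithmetic | Average over simulated trials |
|---|---|---|
| 0 | 1 × 0.50 = 0.50 | 0.50 |
| 0.25 | 0.75 × 0.50 = 0.375 | 0.37 |
| 0.50 | 0.50 × 0.50 = 0.25 | 0.25 |
| 0.75 | 0.25 × 0.50 = 0.125 | 0.13 |

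The simulation used 8 schools per arm, 16 pupils per school, an intra-school correlation of 0.02 and a = 1. Without engagement in the model, the coefficient averaged 0.50 throughout.

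*Shared cause.* Suppose no effect runs through engagement (s = 0), but an unmeasured school factor accounts for half the variance of engagement and all the between-school variance of the outcome. The slope on engagement is then √0.02 × √0.5 = 0.141 × 0.707 = 0.10, and the group coefficient moves to 0.50 − a × 0.10 = 0.40 at a = 1. The simulated average was 0.40.

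*Precision.* In equal arms, the squared correlation of E with arm is r² = 0.25a² / (0.25a² + 1), and the standard error is multiplied by 1/√(1 − r²):

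- a = 1: r² = 0.25/1.25 = 0.20; variance inflation 1/0.80 = 1.25; standard error × √1.25 = 1.12.
- a = 2: r² = 1/2 = 0.50; variance inflation 1/0.50 = 2.0; standard error × √2 = 1.41.

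These factors hold at a fixed residual variance. Where engagement explains outcome differences between schools, part of the loss is offset or reversed. At a = 1 and s = 0.5, the empirical SD of the estimate went from 0.192 without engagement to 0.173 with it. The main cost is therefore bias.

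**3. The other listed variables.** A parking indicator equal to 1 for every school duplicates the intercept: intercept, group and parking give 3 columns of rank 2. The term drops out and the group coefficient is unchanged. Weather in Phase II comes from the station nearest each school (2.7.2.19), and lane length is a GIS measure (2.7.2.20). Allocation changes neither, so the arm-to-mediator path is zero by design. Lane length is also an adjuster in the same paragraph.

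**The case against.** The best reply concerns timing. A baseline engagement rating is planned before the draw, section 2.7.2.20 does not confine engagement to intervention schools, and adjusting for that baseline rating would be legitimate. This stands, and it limits the point: the fault lies in an adjuster worded as engagement in the intervention, with the baseline rating not named. It does not follow that engagement must be dropped in every form.

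Several stronger readings are tempting but not supported:

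- *Engagement is nearly collinear with arm.* The protocol gives no distribution of the score in either arm. A 1 SD difference inflates the standard error only 1.12-fold.
- *No school-level degrees of freedom remain.* A reader might count six schools, the fewest that allow both arms in each of three cities. The readable text gives no number of schools, and section 2.4.2 allows as many as necessary. The same count would also defeat a sensible model: intercept, group, two city terms, area socioeconomic status and lane length already make six.
- *Control schools receive nothing.* They are offered the programme after the eight weeks; only the comparison period is programme-free.
- *The parking term biases the result.* A constant covariate is harmless. Rack location, which section 2.7.2.20 records as on the premises or near the entrance, might vary, but availability is what the analysis section names.
- *Weather and built environment are declared mediators.* The text calls them covariates included in the mediation analysis, and such a model may carry covariates that do not mediate. What stands is that no roles are assigned and that these variables cannot be mediators.

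**Conclusion.** The point holds for engagement. As worded, section 2.10.2 conditions the group effect on a variable that allocation influences, and this can bias the estimates for the main outcomes. The direction is attenuation if engagement carries part of a beneficial effect, with further bias if engagement and outcome share causes. The figures of 0.37, 0.25 and 0.13 for a true 0.50 SD, and of 1.12 and 1.41 for the standard error, show what the mechanism does under assumed values and do not forecast this trial. If no effect ran through engagement and no unmeasured factor drove both, the coefficient would stay at 0.50. If the authors meant the baseline rating, one clarifying phrase settles the matter.

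Parking and the mediation list are secondary. The first is uninformative but does no harm. The second needs roles assigned before its results can be interpreted.

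**What to change.** In section 2.10.2:

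- Restrict adjusters in the effect model to variables fixed before the draw: the baseline outcome, city, area socioeconomic status, cycling-lane length and, if it is defined for all schools, the baseline engagement rating of section 2.7.2.20. Keep the number of school-level terms in proportion to the number of schools enrolled.
- Report engagement in the intervention as implementation or process data, outside the effect model.
- Delete availability of bicycle parking from the adjuster list.
- Limit mediators to variables the intervention can change, such as body composition, fitness, perceived barriers and autonomy. Use weather and built environment only as effect modifiers or precision covariates, and say which.

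The cost is analysis wording only. No extra data are needed, because the baseline engagement rating is already planned.

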**Method:**

For Phase I, a convenience sample of ~50 adolescents will be recruited. These participants will have their PAEE assessed in three different modes of commuting. Regarding phase II, a total of 300 adolescents from different schools in three Spanish cities will participate in this cluster randomized controlled trial. As many schools as necessary to meet the target sample will be included. In addition, each school will be randomized as either an intervention or control group. Participants from intervention schools will be asked to complete a school-based cycling intervention, while participants from control schools will be asked to continue their same habits for 8 weeks. The school-based cycling intervention will last for 8 weeks and will include *Bikeability* sessions, along with encouragement strategies to increase adherence to cycling to and from school.

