##### Weather

2.7.2.19

Ambient and weather conditions will be assessed using two complementary methods. In Phase I, ambient temperature will be measured using iButtons (S-1922 L, Thermochron; resolution: 0.0625°C; Maxim, Dallas, USA). Participants will wear an iButton attached to their trousers to measure outdoor temperature. It is important to note that the iButton device has also demonstrated a very high correlation with a mercury thermometer (r > 0.999) for measuring ambient temperature (REF). Data from the iButtons will be analyzed using the Temperatus software (see Footnote 2) (90). In Phase II, temperature (maximum, minimum, and average), total rainfall, and average wind speed will be obtained from the National Weather Data Bank. This open-source database contains climatological information recorded by observatories across the country. Data will be collected from the weather station closest to each school for the five weekdays and the preceding weekend prior to completing the student questionnaire. These variables will be recorded at both baseline and follow-up. The main variables of interest include daily ambient temperature (°C), total rainfall (mm), and average wind speed (km/h). Data will be aggregated by participant and city.

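### The standardised effect is defined as follow-up minus baseline and effect sizes are then graded, with no between-arm standardised effect defined, so shared change could be labelled an intervention effect

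*Protocol article*

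**What the plan says.** Section 2.10.2 (Statistical analysis) makes three statements about Phase II effects.

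- **The model.** Post-intervention values are the dependent variable in an ANCOVA, with "group (i.e., experimental group vs. control group) as fixed factor, and baseline outcome data as covariates". This is a between-arm contrast.
- **The scale.** Estimates are to be shown raw and standardised. Standardised is explained in parentheses as "z-scores; i.e., mean differences between follow-up and baseline data divided by the standard deviation". The same sentence adds that "post-intervention z-scores will be calculated relative to the baseline mean and standard deviation", and describes this as indicating change.
- **The grading.** "Effect sizes will be categorized as small (0.2 SDs), medium (0.5 SDs), and large (0.8 SDs), based on Cohen".

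The section defines no other standardised quantity for Phase II. It does not say which SD is the divisor in the parenthesis, or whether the baseline mean and SD are pooled or taken by arm.

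Elsewhere the comparison is between arms. The last paragraph of the Introduction states the hypothesis against a control group, the sample-size section (2.4.2) is built on two comparison groups, and in the abstract "participants from control schools will be asked to continue their same habits for 8 weeks".

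**The concern.** A follow-up minus baseline difference measures change over time. Allocation is not among its inputs. If that is what receives the small, medium or large label, the label answers a different question from the ANCOVA and from the hypothesis.

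Shared change is plausible here. Participants are 12 to 17 years old (Table 2), fitness and motor tests are repeated at both assessments, and the protocol treats weather as relevant enough that "These variables will be recorded at both baseline and follow-up". The concurrent control arm is there to remove such change, and a within-arm standardised change does not use it.

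Two errors could follow. With no treatment effect, a common upward change could be labelled a small or medium effect. With a real benefit, a common downward change could pull the label towards none. The labels would cover the primary outcomes and a long list of secondary ones, and readers may remember a label better than the model estimate beside it.

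**Working it through.** The plan states no figure that rests on this definition, so there is none to reproduce. The check applies the written definition and compares it with the ANCOVA contrast on the same scale.

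**Inputs from the protocol**
- Definition, model and thresholds: section 2.10.2.
- n = 125 per arm: half of the 250 participants stated as needed in section 2.4.2.

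**Assumptions not in the protocol**
- Baseline to follow-up correlation r = 0.8, with 0.6 as an alternative.
- Equal SDs at baseline and follow-up, both set to 1.
- Shared change d in both arms, varied, because the documents give no value.
- No clustering.

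**Step 1: what each quantity estimates.** Let the true treatment effect be e, in SD units.
- Written definition, intervention arm: mean = d + e. Control arm: mean = d.
- ANCOVA group coefficient on z-scores with one common baseline mean and SD: mean = e. The shared change goes into the intercept.

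The two agree on average only if d = 0. Examples:
- d = 0.3, e = 0: written 0.30 (small); between arms 0.00.
- d = 0.5, e = 0: written 0.50 (medium); between arms 0.00.
- d = 0.3, e = 0.2: written 0.50 (medium); between arms 0.20 (small).
- d = −0.2, e = 0.2: written 0.00 (no label); between arms 0.20 (small).

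**Step 2: chance of at least a small label in the intervention arm when e = 0.**

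SE of the within-arm standardised change = √(2(1 − r)/n).
- r = 0.8: √(2 × 0.2/125) = 0.057.
- r = 0.6: √(2 × 0.4/125) = 0.080.

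P(change ≥ 0.2) = 1 − Φ((0.2 − d)/SE):

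| Shared change d | r = 0.8 | r = 0.6 |
|---|---|---|
| 0.1 SD | 4% | 11% |
| 0.2 SD | 50% | 50% |
| 0.25 SD | 81% | 73% |
| 0.3 SD | 96% | 89% |

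**Step 3: the same threshold applied to the between-arm contrast when e = 0.**

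SE = √(2(1 − r²)/125).
- r = 0.8: √(2 × 0.36/125) = 0.076; P(difference ≥ 0.2) = 0.4%.
- r = 0.6: √(2 × 0.64/125) = 0.101; P(difference ≥ 0.2) = 2.4%.

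Neither depends on d. Clustering would raise both. With an assumed design effect of 2, the SEs become 0.076 × √2 = 0.107 and 0.101 × √2 = 0.143, and the probabilities about 3% and 8%.

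**Step 4: check by simulation** (2,000 trials, 125 per arm, r = 0.8, e = 0, no clustering). At d = 0.3, the within-arm value reached 0.2 in 95% of trials and the ANCOVA contrast in 0.5%. At d = 0, the figures were 0.2% and 0.9%, so without shared change the written definition does no harm in this respect.

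**The case against.** The strongest reply is that the estimates in question are the ANCOVA estimates, since no other Phase II estimates come before that sentence. On this view the z-score clause only describes the scale: post values are centred and scaled by the baseline mean and SD, and then enter the model. With a common baseline reference, the group coefficient would be the between-arm difference in baseline SD units, and shared change would cancel. This reading is possible, and it is why a flat claim that the plan ignores the control arm would go too far. It does not rescue the wording, because the parenthesis defines the standardised estimate as follow-up minus baseline, and an analyst who follows it would compute change over time.

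Other parts of the reply also stand.
- The grading sentence does not name the quantity it grades. The link to the sentence before it is an inference, though no other standardised quantity is available.
- The plan does not say that only the intervention arm would be graded. If both arms were shown, a shared change would be visible in the controls.
- The illustrative percentages depend on d. A change of 0.2 SD meets a 0.2 SD threshold half the time by construction, and at 0.1 SD with r = 0.8 the figure is only 4%. The protocol gives neither size nor direction for any trend, and no calendar from which to infer one.
- The between-arm figures without clustering flatter the alternative, as step 3 shows.

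A journal article may leave effect-size formulae to a fuller plan. Here, however, the article states a formula, and it does not match its own model and hypothesis.

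**Conclusion.** The point holds for the standardised estimate and its label. As written, the only standardised quantity defined has no control-arm term, and effect sizes are graded directly afterwards. Shared change could therefore be labelled an effect, or could mask one.

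A reader might infer that the trial's test of the intervention is uncontrolled, or that false claims of effect are likely. The documents support neither. The ANCOVA, its p-value and the raw group difference compare the arms under any reading, and no sample-size or decision rule depends on the labels. Nor do the documents show that a shared change of 0.2 to 0.3 SD will occur in 8 weeks.

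The size is conditional. With no treatment effect, n = 125, r = 0.8 and clustering ignored, the chance of at least a small label runs from about 4% at 0.1 SD of shared change to 96% at 0.3 SD. The sentence should be corrected before analysis. Confidence is medium, because the authors may have meant the between-arm quantity.

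**What to change.** Replace the definition in section 2.10.2 with:

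*Standardised effects are the baseline-adjusted between-group difference at follow-up (intervention minus control) from the ANCOVA, divided by the pooled baseline SD, with a 95% CI that accounts for school clustering. The 0.2/0.5/0.8 labels apply only to this quantity. Within-group change is descriptive and is not graded.*

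This suits either reading: it corrects the definition if within-arm change was meant, and makes it explicit if the between-arm effect was meant. It needs no new data. The cost is one sentence, and some reported effect sizes may be smaller than within-arm changes would have been.
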